## Abstract

**Background:**

Low back pain is a major clinical and public health problem, with limited evidence-based treatments. Low-dose antidepressants are commonly used to treat pain in chronic low back pain. However, their efficacy is unproven. The aim of this pragmatic, double-blind, randomised, placebo-controlled trial is to determine whether low-dose amitriptyline (an antidepressant) is more effective than placebo in reducing pain in individuals with chronic low back pain.

**Methods/design:**

One hundred and fifty individuals with chronic low back pain will be recruited through hospital and private medical and allied health clinics, advertising in local media and posting of flyers in community locations. They will be randomly allocated to receive either low-dose amitriptyline (25 mg) or an active placebo (benztropine mesylate, 1 mg) for 6 months. The primary outcome measure of pain intensity will be assessed at baseline, 3 and 6 months using validated questionnaires. Secondary measures of self-reported low back disability, work absence and hindrance in the performance of paid/unpaid work will also be examined. Intention-to-treat analyses will be performed.

**Discussion:**

This pragmatic, double-blind, randomised, placebo-controlled trial will provide evidence regarding the effectiveness of low-dose antidepressants compared with placebo in reducing pain, disability, work absenteeism and hindrance in work performance in individuals with chronic low back pain. This trial has major public health and clinical importance as it has the potential to provide an effective approach to the management of chronic low back pain.

**Trial registration:**

Australian New Zealand Clinical Trials Registry: ACTRN12612000131853; registered on 30 January 2012.

**Electronic supplementary material:**

The online version of this article (doi:10.1186/s13063-016-1637-1) contains supplementary material, which is available to authorized users.

## Background

Low back pain is a major public health problem worldwide. It is one of the most widespread health conditions, with a lifetime prevalence of more than 70 % in industrialised countries [1]. It is also the leading cause of disability globally, with estimates indicating that it is responsible for 83 million years lived with disability [2]. Moreover, low back pain is associated with substantial socioeconomic burden due to disability and productivity losses, with annual costs of AU$9.17 billion in Australia [3] and US$91 billion in the United States [4]. Although low back pain results in huge personal and socioeconomic costs, effective evidence-based treatments are limited.

Drug therapy is one of the treatment options available for chronic low back pain. Antidepressants are commonly prescribed in low back pain to treat depression, sleep and pain and their use is increasing for the treatment of low back pain [5]. Two main groups of antidepressants are used in the treatment of low back pain, tricyclic antidepressants (TCAs) and selective serotonin reuptake (SSRIs) inhibitors. While the mechanism of action of these antidepressants is not fully understood, their effect is attributed to inhibition of the reuptake of serotonin and/or noradrenaline in the central nervous system [6]. However, there is evidence to indicate that TCAs and SSRIs have an effect on the endogenous opioid system and can also act peripherally [7]. These mechanisms are thought to be important in targeting central sensitisation in chronic low back pain, where an abnormal state of responsiveness or increased gain in the nociceptive system occurs and neurons activated by nociceptive stimulus are sensitised and become hyperresponsive to subsequent stimuli [8]. Thus, antidepressants, at significantly lower doses (25–50 mg) than those which are used for depression (100–300 mg) are used in clinical practice to treat pain [6, 9]. In addition, the analgesic effect of low-dose antidepressants has been shown to be independent of their mood-altering effect [10].

Several systematic reviews have examined the efficacy of antidepressants in the management of chronic low back pain [11–13]. However, these reviews have reached different conclusions. A Cochrane systematic review and meta-analysis, which evaluated the effectiveness of TCAs (seven studies), SSRIs (three studies) and ‘atypical’ antidepressants (two studies), concluded that there is no clear evidence to indicate that antidepressants are more effective than placebo in reducing pain in individuals with chronic low back pain [14]. Moreover, pooled analyses showed no difference in pain relief between different types of antidepressants and placebo. However, a high-quality trial by Atkinson [15], which performed a head-to-head comparison of TCAs and SSRIs, reported a greater reduction in pain intensity with a low concentration of a TCA than with all concentrations of a SSRI. The authors concluded that the Cochrane review was limited by a paucity of trials, in particular those examining low-dose antidepressants, small study populations and variation in study quality and individuals recruited. Further trials were recommended to confirm the efficacy of antidepressant therapy for chronic low back pain. Thus, the role of antidepressants in low back pain is unclear and although low-dose antidepressants are a common treatment for chronic low back pain, their use is still unproven for the treatment of pain.

We propose a pragmatic, double-blind, randomised, placebo-controlled trial to determine whether a low-dose TCA (amitriptyline) is effective in reducing pain. It is hypothesised that low-dose amitriptyline will improve pain in individuals with chronic low back pain. If it is found to be effective, it will provide high-quality evidence for its use and potentially enable this treatment option to be considered by more individuals with chronic low back pain. If we do not find low-dose amitriptyline to be effective, then our trial will provide strong evidence to reconsider its use in the management of chronic low back pain.

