## Methods

### Study design

This study is a double-blind, randomised, placebo-controlled trial, with a two-arm, parallel group, superiority design. The trial was registered at the Australian New Zealand Clinical Trials Registry prior to recruitment (ACTRN: ACTRN12612000131853) and trial reporting will be guided by the Consolidated Standards of Reporting Trials (CONSORT) [16] and Standard Protocol Items: Recommendations for Interventional Trials (SPIRIT) guidelines (See Additional file 1). Ethics approval has been obtained from the Alfred Hospital Ethics Committee (HREC/12/Alfred/16, 476/11), Monash University Human Research Ethics Committee (CF12/0271 - 2012000106) and the Eastern Health Human Ethics Committee (SERP28/1112).

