### Randomisation and blinding

Randomisation will be based on computer-generated random numbers prepared by a statistician who will have no involvement in the trial. The allocation of participants will be in a 1:1 ratio to either the intervention or the control group. The use of a central allocation which involves pharmacy-controlled randomisation will ensure that the allocation cannot be accessed or influenced by any of the research personnel. The randomised controlled trial (RCT) will be double-blinded, with both participants and investigators assessing outcomes blinded to treatment allocation. Allocation concealment and double blinding will be ensured by (1) the medications being dispensed by the hospital clinical trial pharmacy, (2) the use of an identical active placebo tablet which mimics the side-effects of amitriptyline and (3) questionnaire data that is subjectively being taken by research assistants blinded to group allocation.

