#### Primary outcome measures: pain intensity

Our primary outcome measure will be pain intensity measured at 6 months using a Visual Analogue Scale (VAS) of 100 mm. However, the Descriptor Differential Scale, a valid measure of pain intensity, will also be assessed [25]. The Descriptor Differential Scale has been used in a previous trial of antidepressants in low back pain [15], enabling calculation of study sample size and comparison of results.

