### Sample size calculation

#### Reduction in pain intensity

A previous clinical trial of TCAs in individuals with chronic low back pain reported the mean (standard deviation (SD)) pain scores measured on the VAS to reduce to 5.70 (2.43) in the placebo group (*n* = 48) [34]. With *n* = 56 in each arm of the study, we have 90 % power to detect a difference of 1.5 (i.e. VAS to reduce to 4.20 (2.43) in the treatment group), which reflects the minimum clinically significant reduction in pain intensity (*α* = 0.05, two-sided significance).

In a recent study of individuals with low back pain, the control group (*n* = 22) had a pain score that reduced to a mean (SD) = 6.2 (2.8) on the Descriptor Differential Scale following treatment, while the pain score of the treatment group (TCA) (*n* = 19) reduced to a mean (SD) score = 4.5 (2.6) [15]. With an *α* = 0.05 and *n* = 60 in each arm of the study, we have 90 % power to detect a difference of this size (1.7), which reflects clinically significant reductions in pain intensity from ‘moderate’ to ‘mild’ or from ‘strong’ to ‘moderate’, which is equivalent to a decrease of 2 units (17 %) on the Descriptor Differential Scale (0–12 per descriptor) [35].

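### The Background counts any failure to find benefit as strong evidence to reconsider the drug, but at the planned precision a null result need not exclude the trial's own 1.5-unit important difference

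*Protocol article*

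**What the plan says.** The last paragraph of the Background states in advance what each result would mean. For a negative result it says: "If we do not find low-dose amitriptyline to be effective, then our trial will provide strong evidence to reconsider its use". The only trigger is that the drug is not found effective. No interval, margin or level of precision is mentioned.

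The other relevant statements are:

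- Study design: the trial is set up "with a two-arm, parallel group, superiority design". The article states no equivalence or futility margin.
- Primary outcome: "Our primary outcome measure will be pain intensity measured at 6 months using a Visual Analogue Scale (VAS) of 100 mm".
- Sample size calculation, Reduction in pain intensity: with 56 "in each arm of the study, we have 90 % power to detect a difference of 1.5", a difference "which reflects the minimum clinically significant reduction in pain intensity". The SD is 2.43 in both arms ("VAS to reduce to 4.20 (2.43) in the treatment group") and the test level is "0.05, two-sided significance".
- Improvement in disability: 60 per arm are needed, and 75 per arm (150 in total) will be recruited to allow for at most 20% dropout. Adjustment for baseline is expected to raise power above 90%, but no baseline–follow-up correlation is given.

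**The concern.** In a superiority trial, not finding an effect ordinarily means that the confidence interval for the difference includes zero. That alone does not show that a worthwhile effect is absent. For that, the interval must also exclude the smallest effect that matters, and the article supplies that value: 1.5 units.

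If a null result can leave 1.5 inside the interval, the Background promises a conclusion that the data would not support in that case. The article describes low-dose antidepressants as commonly used for this condition, so a negative reading could influence practice while the trial's own interval still contained a benefit that its authors call clinically significant.

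**Working it through.** **Inputs from the article.** Important difference 1.5; SD 2.43 per arm; two-sided 5% level; 1:1 allocation; 56 per arm (VAS calculation), 60 per arm (after dropout), 75 per arm (recruited).

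**Assumptions.** The sample size section uses scores such as 5.70 and 4.20 while the outcome is on a 100 mm scale, so 1.5 units is read as 15 mm. Not found effective is read as a 95% CI that includes 0. Baseline adjustment with correlation r multiplies the SD by √(1 − r²). The article gives no r, so a range is shown. Benefit is counted as positive.

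**Step 1: reproduce the plan's figures.** n per arm = 2 × (1.960 + 1.282)² × 2.43² / 1.5² = 55.2, rounded up to 56. This matches; power at 56 is 0.904 (0.899 using the t distribution). Allowing for dropout, 60 / 0.8 = 75 per arm, or 150 in total, which also matches.

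**Step 2: half-width of the interval.** SE = SD × √(2/n) × √(1 − r²) and h = t(0.975) × SE. At 60 per arm and r = 0, SE = 2.43 × √(2/60) = 0.444 and h = 1.980 × 0.444 = 0.88.

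**Step 3: when does a null result still include 1.5?** The estimate must be below h (non-significant) and above 1.5 − h (upper limit beyond 1.5). Such estimates exist whenever 2h > 1.5, and 2h is the highest upper limit a null result can have.

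| Analysed per arm | r | SE | h | Highest upper limit, 2h | Null estimates whose CI includes 1.5 |
|---|---|---|---|---|---|
| 56 | 0 | 0.459 | 0.910 | 1.82 | 0.59 to 0.91 |
| 60 | 0 | 0.444 | 0.879 | 1.76 | 0.62 to 0.88 |
| 60 | 0.3 | 0.423 | 0.838 | 1.68 | 0.66 to 0.84 |
| 60 | 0.5 | 0.384 | 0.761 | 1.52 | 0.74 to 0.76 |
| 60 | 0.6 | 0.355 | 0.703 | 1.41 | none |
| 75 | 0 | 0.397 | 0.784 | 1.57 | 0.72 to 0.78 |
| 75 | 0.3 | 0.379 | 0.748 | 1.50 (1.496) | none |

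**Step 4: where it stops.** Setting 2h = 1.5 gives √(1 − r²) = 0.75 / h₀, where h₀ is the half-width at r = 0. At 60 per arm, 0.75 / 0.879 = 0.853, so r ≈ 0.52. At 56 per arm, r ≈ 0.57. At 75 per arm, 0.75 / 0.784 = 0.957, so r ≈ 0.29.

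**Step 5: how often.** For true benefit δ, the chance of a null result whose CI includes 1.5 is Φ((h − δ)/SE) − Φ((1.5 − h − δ)/SE). At 60 per arm, r = 0 and δ = 0, this is Φ(1.98) − Φ(1.40) = 0.976 − 0.919 = 0.057.

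| True benefit (60 per arm) | r = 0 | r = 0.3 | r = 0.5 |
|---|---|---|---|
| 0 | 5.7% | 3.5% | 0.3% |
| 0.5 or 1.0 | 19.5% | 13.9% | 1.8% |
| 0.75 | 22.8% | 16.5% | 2.3% |

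Among non-significant results at r = 0, the share that fails to exclude 1.5 is 6% if the true effect is 0 and 37% if it is 0.75.

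**Step 6: why this happens at 90% power.** A difference detectable with 90% power is about 1.96 + 1.28 = 3.24 SE. A result just short of significance has an upper limit near 2 × 1.96 = 3.92 SE, which is larger. Without adjustment, every null result would exclude 1.5 only at about 97.5% power: n = 2 × 3.92² × 2.43² / 1.5² = 80.7, or 81 analysed per arm.

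**The case against.** The strongest reply is that the sentence is not an analysis rule. It closes the Background as a statement of the trial's value. The Statistical analysis section sets no rule that non-significance means the drug is ineffective, and the non-significance trigger is an inference from the superiority design. To reconsider a treatment is also weaker than to reject it. All of this stands and limits the weight of the point. A reader might infer that the analysis plan itself equates a non-significant test with no effect; the documents do not say so. What remains is that this printed sentence claims strong evidence, with no condition, from not finding an effect.

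The second reply is that the unadjusted figures are unfavourable. The planned analysis adjusts for baseline, 20% is the maximum expected dropout, and those who withdraw are asked to complete the remaining outcome measures. This also stands. At r = 0.5 and 60 per arm, the upper limit passes 1.5 by only 0.02 units, and at slightly higher correlations the problem is gone. But the article gives no correlation, and a larger SD or heavier attrition would bring the problem back.

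The third reply is that if the drug truly does nothing, the trial will usually exclude 1.5. That is right: at r = 0 only about 6% of null results would fail to do so. The amended wording keeps the strong negative conclusion whenever 1.5 is excluded.

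**Conclusion.** The point holds as a matter of wording. On the article's own SD and 60 analysed per arm, a non-significant result can leave the 1.5-unit important difference inside its 95% CI, with an upper limit of up to 1.76 unadjusted, 1.68 at r = 0.3 and 1.52 at r = 0.5. With no baseline correlation the chance is about 6% if the true effect is 0 and 20–23% for true benefits of 0.5–1.0. It falls to nothing above r of about 0.52, or about 0.3 if all 75 per arm are analysed.

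A reader might infer that the trial is underpowered or its sample size wrong. The documents do not support that: 56 and 75 per arm both reproduce. Nor does it follow that a negative conclusion would usually be mistaken. Only the unconditional form of the inference is unsupported. The size rests on SD 2.43, the reading of 1.5 units as 15 mm, and a correlation that the article does not give.

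**What to change.** State, in the analysis plan or the reporting plan before unblinding, that:

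- a null result supports the strong conclusion in the Background only if the baseline-adjusted 95% CI for the 6-month VAS difference lies wholly below a 15 mm benefit;
- a CI that includes both 0 and a 15 mm benefit is inconclusive.

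If a rule for a positive result is stated alongside, it should require the CI to exclude 0 in the direction of benefit, so that an interval on the harm side cannot count as success. The result should also be reported against 15 mm, so that a significant benefit smaller than that is not called clinically important.

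This changes wording only. It needs no extra participants, leaves the primary analysis as it is, and uses the trial's own threshold. The downside is that some null results will have to be called inconclusive.

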## Methods

### Study design

This study is a double-blind, randomised, placebo-controlled trial, with a two-arm, parallel group, superiority design. The trial was registered at the Australian New Zealand Clinical Trials Registry prior to recruitment (ACTRN: ACTRN12612000131853) and trial reporting will be guided by the Consolidated Standards of Reporting Trials (CONSORT) [16] and Standard Protocol Items: Recommendations for Interventional Trials (SPIRIT) guidelines (See Additional file 1). Ethics approval has been obtained from the Alfred Hospital Ethics Committee (HREC/12/Alfred/16, 476/11), Monash University Human Research Ethics Committee (CF12/0271 - 2012000106) and the Eastern Health Human Ethics Committee (SERP28/1112).

### Participants

A total of 150 individuals with chronic low back pain will be recruited through hospital and private medical and allied health clinics, advertising in local media including national newspapers and community magazines, and posting of flyers in community locations such as shops, libraries and medical clinics. Written informed consent will be obtained from all participants by research staff trained in study procedures specific to this trial.

### Inclusion criteria

We will recruit male and female participants aged 18–75 years with chronic, nonspecific low back pain, which is defined as pain between the lower borders of the rib cage and the gluteal folds, is without a specific cause and has been present for longer than 3 months [17, 18].

### Exclusion criteria

Participants with any of the following will be excluded: (1) specific pathological entity, such as infection, metastasis, osteoporosis or fractures, (2) major coexisting illness which might confound assessment of function or for which amitriptyline may be inappropriate (e.g. heart or thyroid problems, glaucoma, seizures, urinary issues), (3) another significant musculoskeletal condition, (4) history of psychosis, (5) current or previously diagnosed depression with or without the use of medication), (6) any prior or current use of antidepressants, (7) current use of opioids, (8) any contraindication or allergy to amitriptyline, (9) pregnancy, planning or trying to become pregnant or breastfeeding or (10) inability to give informed consent, including individuals that are unable to read, speak or understand English.

### Randomisation and blinding

Randomisation will be based on computer-generated random numbers prepared by a statistician who will have no involvement in the trial. The allocation of participants will be in a 1:1 ratio to either the intervention or the control group. The use of a central allocation which involves pharmacy-controlled randomisation will ensure that the allocation cannot be accessed or influenced by any of the research personnel. The randomised controlled trial (RCT) will be double-blinded, with both participants and investigators assessing outcomes blinded to treatment allocation. Allocation concealment and double blinding will be ensured by (1) the medications being dispensed by the hospital clinical trial pharmacy, (2) the use of an identical active placebo tablet which mimics the side-effects of amitriptyline and (3) questionnaire data that is subjectively being taken by research assistants blinded to group allocation.

### Intervention

Participants in the intervention arm will receive a TCA, 25 mg of amitriptyline (Alphapharm Pty Ltd., Miller’s Point, NSW, Australia), and those in the control arm will receive an active placebo, 1 mg benztropine mesylate (Phebra Pty Ltd., NSW, Australia). Amitriptyline and benztropine will be administered in identical capsules to be taken in a single dose at the same time each day. We selected low-dose amitriptyline as it is commonly prescribed for the management of chronic pain [19]. It has been reported to be the most effective antidepressant for the treatment of neuropathic pain, such as diabetic neuropathy and neuralgia [20], and is also effective for various pain conditions, including fibromyalgia [7], ankylosing spondylitis [21] and headaches [22]. Amitriptyline can act on pain independent of depression [10], and while side effects, such as dry mouth, mild constipation and fatigue, can occur, lower doses are used for pain modification and are generally well-tolerated. We have selected benztropine, an active placebo, as it mimics the side effects of amitriptyline, such as dry mouth and constipation, while having no known effect on chronic pain [23, 24]. All participants will be provided with usual care by their treating health practitioners.

### Study procedure

The study procedures are presented in Fig. 1. Potential participants will be initially screened over the phone using a questionnaire to determine whether they meet the eligibility criteria. They will then attend an initial assessment at Monash University Department of Epidemiology and Preventive Medicine with the aim of obtaining informed consent and confirming the individual’s eligibility to participate in the trial. Eligible participants will be randomised, complete a baseline assessment and receive the first 3 months of amitriptyline or benztropine from the Alfred Hospital Clinical Trials Pharmacy. Participants will be contacted by phone at 2 weeks, 1–2 months, 3 months, 4–5 months and 6 months to monitor their progress and any side effects of the treatment. The 3- and 6-month outcome questionnaires and the second 3 months of medication will be posted to the participants by mail. The same researchers, who are blinded to treatment allocation, will measure all clinical variables, administer questionnaires, monitor compliance and record adverse events. Unblinding will be allowed under certain circumstances, such as a participant’s physician requiring their allocated intervention to ensure that they receive the appropriate medical care. Compliance by trial medication will be assessed by pill count. Participants will not be paid for their participation in the trial, but they will be reimbursed for parking and transport costs.

